### Patient inclusion and exclusion criteria

All acute ischaemic stroke patients ≥ 18 years admitted within 4½ hours of symptom onset may be included in the study. An intracranial arterial occlusion on pre-treatment computed tomography angiography (CTA) is not a prerequisite for inclusion since this study also includes sonothrombolysis/sonolysis of the peripheral vascular bed and central perforating arteries. Study participation is based on informed consent requirements as approved by the ethics committee. Exclusion criteria are listed in Table 1.

**Table 1 Tab1:** Inclusion and exclusion criteria

Inclusion criteria
•Patients >18 years with acute ischaemic stroke, with or without a visible arterial occlusion, and start of treatment within 4 ½ hours after stroke onset.
General exclusion criteria
•Patients with premorbid modified Rankin Scale (mRS) score ≥3
•Patients for whom a complete NIH Stroke Score cannot be obtained
•Hemiplegic migraine with no arterial occlusion on baseline CT
•Seizure at stroke onset and no visible occlusion on baseline CT
•Intracranial haemorrhage on baseline CT
•Clinical presentation suggesting subarachnoid haemorrhage even if baseline CT is normal
•Large areas of hypodense ischaemic changes on baseline CT
Patients with primary endovascular treatment
•Pregnancy or breast feeding, pericarditis, sepsis, any other serious medical illness likely to interact with treatment, confounding pre-existent neurological or psychiatric disease, unlikely to complete follow-up, any investigational drug <14 days
Specific sonothrombolysis/sonolysis exclusion criteria
•Known hypersensitivity or allergy to SonoVue®
•Recent or unstable coronary ischemia or resting angina <7 days
•Acute cardiac insufficiency, cardiac insufficiency class III/IV; serious cardiac arrhythmias
•Any right-left-shunt, severe pulmonary hypertension (PAP >90 mmHg) Moderate to severe chronic obstructive pulmonary disease (chronic obstructive pulmonary disease (COPD), baseline O2 saturation <80 %)
•Acute respiratory distress syndrome (ARDS)

### Study endpoints

Primary study endpoints are 1) neurological improvement (NIHSS score) at 24 h (clinical effect; proof of concept) and 2) functional handicap defined as modified Rankin Scale (mRS) score 0–1 at 90 days (clinical outcome). Secondary study endpoints are 1) haemorrhagic transformation (haemorrhagic infarct/haematoma), 2) symptomatic cerebral haemorrhage (safety endpoint), 3) recanalisation at 2 h (optional), 4) recanalisation at 24–36 h, 5) MR-DWI lesion volume at 24–36 h and 6) death.

### Assessment methods

Table 2 neurological deficit is documented with National Institutes of Health Stroke Scale (NIHSS). Function is documented with mRS and Barthel Index (BI). On admission, native computed tomography (CT) with CTA is performed for all patients within the therapeutic time window. Early CT ischaemic signs are semi-quantitatively assessed using the ASPECTS scoring system [49]. Intracranial middle cerebral artery (MCA) occlusions are trichotomised in none, distal (MCA_2_), or proximal (MCA_1_) occlusion. Other occlusions are defined as appropriate. Intracranial artery stenosis are described as minor (≤50 %), moderate (51-70 %) and severe (71-99 %) diameter reduction or occlusion. Magnetic resonance imaging and angiography (MRI/MRA) or CT/CTA is performed after 22–36 h to verify the infarct, assess intracranial recanalisation and to detect haemorrhagic transformation. Radiological assessment is performed by investigators blinded to the treatment given. Duplex ultrasound examinations are carried out the day after admission. Carotid stenosis grading is based on flow velocities calculated with a modified NASCET formula or with the internal-common carotid ratio (IC-CC ratio).

**Table 2 Tab2:** Assessment of patients with acute ischaemic stroke admitted ≤4½ hours

Procedure ↓	Timepoint→	Baseline	1-2 h	+24 h (22-36 h)	+48 h (42–54 h)	Day 7 or earlier discharge	Day 90
NIHSS score		X	X	X	X	X	(X)
CT / CTA (MRI / MRA)		X		X			
ECG		X					
Duplex ultrasound of the neck				X			
Transcranial duplex ultrasound		X	X	(X)		(X)	
Modified Rankin Scale (mRS)		X				X	X
Barthel Index (BI)						X	(X)
Check Recurrent stroke / TIA							X
Check Acute coronary heart disease							X

*(X)* optional

The amount of ultrasound delivery to the vasculature cannot be assessed in NOR-SASS. As a surrogate marker for attenuation through the skull, bone window thickness is measured by a physician blinded to clinical information, except for the window of insonation.

### Long-term follow-up

Long-term follow-up is performed by standardised questionnaire as an outpatient clinic visit by a neurologist or as a telephone interview by a study nurse at 3 months. Modified Rankin Score, recurrent vascular events, other diseases or complications, employment state, marriage state, and mood are registered. Death is checked via the Norwegian Public Death Registry.

### Treatment

Patients are treated according to the Department’s Standard Operating Procedure (SOP). Specific intravenous or intra-arterial acute treatment, neurosurgery, and general medical treatment are registered in Norwegian Stroke Research Registry (NORSTROKE). Thrombolytic treatment must start ≤4½ hours after acute ischaemic stroke symptoms onset. Alteplase is given in a dose of 0.9 mg/kg (10 % bolus + 90 % infusion during 1 h), maximum dose 90 mg. Tenecteplase is given in a dose of 0.4 mg/kg as bolus, maximum dose 40 mg.

### Treatment with ultrasound and microbubbles (sonothrombolysis or sonolysis)

In patients without an angiographically defined clot, the investigator judges the clinical picture and applies ultrasound to the region in which she/he thinks the lesion/clot is located, either through the temporal or foraminal window as appropriate. In patients with a defined occlusion, ultrasound is applied to the region of the occlusion. All patients are examined and monitored with transcranial color-coded duplex sonography (TCCS) and transcranial doppler (TCD) performed by an experienced ultrasonographer working independently from the treating physician. Intravenous microbubbles (SonoVue®; 10 ml = 80 μl = 45 μg microbubbles) are given as an infusion of 0.3 ml/min for ~30 min, using a BraccoVueJet® infusion pump (BRACCO Imaging, Switzerland).Baseline TCCS examination is performed to locate the best insonation window, to locate any occlusion and to assess haemodynamics. A temporal bone window is defined as good when it allows good visualisation of standard landmarks such as the mesencephalon. A foraminal window is defined as good when it allows good visualisation of the basilar artery. Bilateral assessment of MCA flow velocities may be undertaken to calculate inter-hemispheric asymmetry indices [50].Sonothrombolysis or sonolysis is performed with 2 MHz pulsed wave TCD monitoring for 60 min, using either a hand-held TCD probe or a probe in a fixation head-band. TCD emitted power output is set at the maximal achievable level with mechanical index MI <1.0. The sound of TCD is muted and the visual display is turned away from the treating physicians and nurse in order to keep them blinded to the patients’ study-group assignment [8, 51]. Insonation is performed with continuous slight “fanning” of the presumed region of interest, with or without the head band.Recanalisation is assessed at 60 min after start of sonothrombolysis or sonolysis with TCCS.

### Treatment with sham sonothrombolysis or sham sonolysis

After baseline diagnostic TCCS, the 2 MHz TCD probe is plugged into an inactive channel. Recanalisation is assessed using active TCCS at 60 min after start of sham sonothrombolysis or sonolysis. Sham intravenous contrast (NaCl 0.9 %) is given as an iv infusion of 0.3 ml/min for ~30 min, using a BraccoVueJet® infusion pump. Care is taken not to display to the treating physicians which infusion is given.

### Outcomes measures

#### Clinical outcome (neurology and function)

Early (2 h and 24–36 h) clinical outcome, short term (day 7, or earlier if earlier discharge) and long term (day 90) functional outcome are assessed in a blinded fashion by a trained stroke nurse or neurologist.

Early clinical outcome is defined by NIHSS score as 1) absolute reduction in NIHSS at 2 h (∆NIHSS_2_ = NIHSS_0_–NIHSS_2_) and at 24 h (∆NIHSS_24_ = NIHSS_0_–NIHSS_24_) and as 2) neurological improvement at 24 h (NIHSS_24_ = 0 or reduction of ≥4 NIHSS points compared with baseline NIHSS_0_). Short term outcome is defined by mRS score using sliding dichotomy/responder analysis (excellent outcome mRS 0 with baseline NIHSS ≤7, mRS 0–1 with baseline NIHSS 8–14, mRS 0–2 with baseline NIHSS ≥15).

Long term outcome is defined by mRS score using 1) single mRS group comparison; 2) fixed dichotomy (excellent = mRS 0–1 vs. unfavourable = mRS 2–6 outcome, and good = mRS 0–2 vs. bad mRS 3–6 outcome); and 3) sliding dichotomy/responder analysis (excellent outcome mRS 0 with baseline NIHSS ≤7, mRS 0–1 with baseline NIHSS 8–14, mRS 0–2 with baseline NIHSS ≥15).

### Vascular outcome (recanalisation)

In patients with a defined arterial occlusion on pre-treatment CTA, early recanalisation is assessed by TCCS at 60 min. Flow is categorised according to the Thrombolysis in Brain Ischaemia (TIBI) grading [52] modified as 0 = absent flow; 1 = minimal flow; 2 = reduced (TIBI 2–3 blunted/dampened) flow; 3 = restored (TIBI 4–5 stenotic/normal) flow.

In patients without a defined arterial occlusion on pre-treatment CTA, haemodynamics are assessed by TCCS at 60 min. In patients with MCA occlusions, inter-hemispheric asymmetry is calculated comparing time averaged mean flow velocities. Significant peripheral MCA obstruction(s) is defined as MCA_1_ mean flow velocities >21 % lower than in the contra-lateral MCA_1_ [50].

Recanalisation at 1 h is by necessity performed unblinded by the investigator. Recanalisation at 24-h is assessed by 24-h MRA (or CTA when MRA is not possible) by a neurologist and/or neuroradiologist blinded to all clinical data [53]. Vascular patency is assessed using adapted Thrombolysis in Myocardial Infarction (TIMI) criteria [54]. Vessel occlusion status is defined as complete occlusion (TIMI 0), minimal flow (TIMI 1), partial flow (TIMI 2), or normal flow (TIMI 3). Major vessel recanalisation is defined as improvement in baseline-24 h TIMI score of ≥2, or complete recanalisation.

### Brain tissue outcome (infarction)

Tissue damage is assessed by 24-h MRI diffusion weighted imaging (DWI) or (CT when MRI is not possible) by a neurologist and/or neuroradiologist blinded to all clinical data, using ASPECTS scoring system [49, 55]. In patients without a visible occlusion on initial CTA the MRI localisation of the lesion is compared with the clinically suspected localisation and will confirm whether the initial ultrasound was aimed at the correct region of interest or not.

### Safety outcome

Patients are monitored in the stroke unit (or intensive care unit (ICU) if appropriate) with NIHSS scoring at close intervals for 24–36 h. Safety is determined by the incidence of haemorrhagic transformation within 24-h of treatment on MRI (or CT when MRI is not possible) by a neurologist and/or neuroradiologist blinded to all clinical data. Classification of haemorrhagic transformation is left to the discretion of the local investigators. In case of disagreement, the scans are assessed by the Data Safety Monitoring Committee.

Haemorrhagic transformation (ECASS criteria) are categorised as *haemorrhagic infarction* 1 (HI1 = small petechiae along the margins of the infarct); *haemorrhagic infarction* 2 (HI2 = confluent petechiae within the infarcted area but no space-occupying effect); parenchymal haemorrhage 1 (*PH1* = blood clots in 30 % or less of the infarcted area with some slight space-occupying effect); p*arenchymal haemorrhage 2 (PH2* = blood clots in more than 30 % of the infarcted area with substantial space-occupying effect); and *Remote parenchymal haemorrhage (rPH =* bleeding outside the infracted area).

Symptomatic cerebral haemorrhage (sICH) is defined as local or remote parenchymal haemorrhage type 2 on the 22–36 h post-treatment imaging scan, combined with a neurological deterioration of 4 points or more on the NIHSS from baseline or from the lowest NIHSS value between baseline and 24 h, or leading to death *(SITS-MOST criteria)* [56]. In order to facilitate comparison with published studies, sICH is also assessed according to 1) NINDS /Cochrane criteria [57] as any haemorrhage plus any neurological deterioration [NIHSS score ≥1] or that leads to death within 7 days; 2) ECASS II criteria [58] as blood at any site in the brain on the CT scan, clinical deterioration or adverse events indicating clinical worsening (drowsiness, increase of hemiparesis) or causing an increase in the NIHSS score of 4 or more points; and 3) ECASS III criteria [59] as any apparently extravascular blood in the brain or within the cranium associated with clinical deterioration (defined by an increase in the NIHSS score of 4 or more points) or death, and that is identified as the predominant cause of the neurological deterioration.

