### Safety monitoring

The over-all rate of bleeding complications will be compared with historical data from the NORSTROKE Registry 2007–2011, the Pooled analysis of iv alteplase trials [57], SITS-MOST [60, 61], ECASS III [59] and series on thrombolysis in patients above 80 years of age [62]. The mortality rate at 7 days will be compared with historical data from NORSTROKE 2007–2011.

All Suspected Unexpected Serious Adverse Reactions (*SUSARs)* are reported to the Norwegian Medicines Agency. All serious adverse events (SAE), i.e., bleedings and deaths, are reported within 24 h to the Executive working group (EWG). The EWG routinely submits a safety report to the independent Data Safety Monitoring Committee (DSMC) after each 40 enrolled patients (20 per group). If the DSMC finds unacceptably increased sICH with CEST+ thrombolysis as compared with sham CEST+ thrombolysis, the study may be stopped for further analysis. If CEST+ tenecteplase shows a 2 % excess of sICH as compared with CEST+ alteplase, the tenecteplase tier may be stopped and the study may be continued with only alteplase patients. The same stopping rule is applied to CES vs. sham CES in patients not eligible for iv thrombolysis.

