Lower frequency ultrasound is theoretically more effective than higher frequency diagnostic ultrasound, because of better penetration through the skull bone windows and stronger thrombolytic effect [65]. The TRUMBI trial (Transcranial Low-Frequency Ultrasound-Mediated Thrombolysis in Brain Ischemia) was a phase II, prospective, multicenter nonrandomized trial that compared standard iv tPA vs. tPA plus low-frequency pulsed-wave transcranial ultrasound (300-kHz) in patients with defined arterial occlusion within a six hour time window. The study was stopped prematurely because of an unexpected high rate of intracerebral bleeding in the group treated with iv tPA and low frequency ultrasound [16]. A technical study which simulated TRUMBI ultrasound delivery, demonstrated that the peak rarefactional pressure was higher than the inertial acoustic cavitation threshold in the presence of standing wave in large areas of the brain, even outside the targeted clot [66] . The technical setting in TRUMBI may therefore have contributed to increased intracerebral bleedings in the ultrasound group.

The TUCSON study (Transcranial Ultrasound in Clinical Sonolysis for acute ischaemic stroke) was a phase I-II, randomised, placebo-controlled, open label, safety, dose-escalation clinical trial which compared iv tPA vs. iv tPA plus 2 MHz ultrasound plus microbubbles in patients with documented intracranial arterial occlusion. The study showed a trend toward higher early recanalisation rate and clinical recovery, but was stopped prematurely by the sponsor, because three patients died in the group treated with iv tPA plus ultrasound plus microbubbles, indicating a possibly increased risk of symptomatic bleedings with this combination [22].

Despite TRUMBI and TUCSON trials results, one experimental animal model of intracerebral hemorrhage showed that ultrasound in combination with microbubbles did not cause additional brain damage during intracerebral hemorrhage [67]. The size of brain hemorrhage, the amount of apoptosis and extension of brain edema was similar between the ultrasound plus microbubbles group and the control group [67]. This was the first experimental study to show that the combination of ultrasound plus microbubbles is safe in cerebral bleedings and may be used in sonothrombolysis and sonolysis studies, even before conventional stroke imaging.

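### The main sICH definition accepts only the 22–36 h scan, so read literally an early fatal type 2 parenchymal haemorrhage does not meet it

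*Protocol article*

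**What the plan says.** Under Safety outcome, the protocol article gives its leading (SITS-MOST) definition: sICH "is defined as local or remote parenchymal haemorrhage type 2 on the 22–36 h post-treatment imaging scan". This must be combined with a worsening of at least 4 NIHSS points from baseline "or from the lowest NIHSS value between baseline and 24 h, or leading to death".

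Under Assessment methods, follow-up MRI/MRA or CT/CTA "is performed after 22–36 h to verify the infarct, assess intracranial recanalisation and to detect haemorrhagic transformation". Table 2 has one follow-up imaging column, at +24 h with the same 22–36 h range. Neither place mentions a scan done earlier because a patient deteriorates.

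The Safety outcome section also opens with a different window: "Safety is determined by the incidence of haemorrhagic transformation within 24-h of treatment on MRI".

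Three further sICH definitions follow, given so that results can be set beside earlier trials. NINDS/Cochrane counts "any haemorrhage plus any neurological deterioration [NIHSS score ≥1] or that leads to death within 7 days". ECASS II starts from blood "as blood at any site in the brain on the CT scan" with clinical worsening. ECASS III takes any extravascular intracranial blood with deterioration or death, where the bleed is the predominant cause of the deterioration.

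Study endpoints labels sICH as the safety endpoint, and lists haemorrhagic transformation and death separately. Safety monitoring then says: "If the DSMC finds unacceptably increased sICH with CEST+ thrombolysis as compared with sham CEST+ thrombolysis, the study may be stopped". It does not say which of the four definitions is meant.

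**The concern.** Of the six secondary endpoints, sICH is the one labelled as safety, and it is the only event named in the stopping provisions. Its leading definition makes one scheduled scan a condition for being counted. A patient who bleeds and dies before that scan cannot satisfy the condition, however clear the bleed was on an earlier scan. The main sICH count could therefore leave out some of the most serious cases.

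The Discussion section shows why fatal bleeds matter for this treatment. It reports that an earlier trial of tPA, ultrasound and microbubbles was stopped "because three patients died in the group treated with iv tPA plus ultrasound plus microbubbles", and reads this as a possible rise in symptomatic bleeding. It gives no timing for those deaths, so it shows that fatal bleeding is of interest here, not that it comes early.

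**Working it through.** The article gives no sICH rate and no power for safety, so there is no figure to reproduce. The check is a literal reading of the definitions.

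**Structure of the leading definition.** It has the form A and (B or C):
- A: PH2, local or remote, on the 22–36 h scan
- B: NIHSS worsening of at least 4 points
- C: the bleed leads to death

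C is an alternative to B. It does not waive A.

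**Test case.** A hypothetical patient deteriorates, has PH2 on an unscheduled CT at 6 h, and dies at 12 h.

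| Rule | Scan window in the text | Test case counted? |
|---|---|---|
| SITS-MOST (leading) | 22–36 h | No: C is met, A is not |
| NINDS/Cochrane | none | Yes: haemorrhage leading to death within 7 days |
| ECASS II | none | Yes: blood on CT with clinical worsening |
| ECASS III | none | Yes, if the bleed is judged the predominant cause |
| Death (secondary endpoint) | none | Yes |
| SAE reporting (bleedings and deaths) | none | Yes |

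Only the leading definition excludes the patient.

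**Neighbouring cases.**
- Early PH2, survives to the 22–36 h scan, still graded PH2: A is met and nothing is lost.
- Early PH2, operated on before 22 h, survives: the scheduled scan can still take place, but the grade may no longer be readable. The outcome is uncertain.
- Death before 22 h with no scan at all: no imaging supports a bleed, and accepting earlier scans would not change that.

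The firm case is therefore PH2 on an early scan followed by death before 22 h.

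**The two windows.** Haemorrhagic transformation is taken within 24 h of treatment; sICH is taken from the 22–36 h scan. If both clocks start at treatment, they overlap only from 22 to 24 h. The 6 h bleed lies inside the first window and outside the second. A finding on a 30 h scan is the reverse if the 24 h limit refers to the time of the scan.

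**Which definition drives stopping.** Safety monitoring uses sICH without qualification. The natural default is the definition that the article gives first, and the text does not assign any of the other three to that role.

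**The case against.** The strongest reply is that the trial does not lose sight of these patients. Three of the four sICH definitions have no scan window, and two of them name death. Haemorrhagic transformation and death are endpoints in their own right. Bleedings and deaths go to the Executive working group within 24 h, and the DSMC receives a safety report after each 40 patients. All of this stands. It rules out the inference that an early fatal bleed is not an sICH in this trial at all, or that the whole safety comparison loses such bleeds.

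A reader might also infer that a harmful signal could pass the DSMC unnoticed. The documents do not support that. The provision for CEST versus sham is discretionary, and nothing makes the committee disregard a reported fatal bleed because of when it was scanned.

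Nor is it sound to measure the loss against the 2 % excess in Safety monitoring. That figure is set for CEST with tenecteplase versus CEST with alteplase, and the same rule is then applied to CES versus sham CES. CEST versus sham has no numerical threshold. With 20 patients per group at a first report, one event is already 1/20 = 5 percentage points.

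Two further arguments are that the definition is a published one, chosen for comparability, and that an article may leave the handling of unscheduled scans to the full protocol or the SAP. The first is met by keeping the strict version as a supplementary figure. The second has some force. But the article does not leave the window open: it states 22–36 h as part of the definition, and that statement conflicts with the evident aim of counting fatal bleeds.

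**Conclusion.** The point holds in a limited form. As written, the leading sICH definition excludes a PH2 bleed in a patient who dies before 22 h. The same patient can qualify under the three supporting definitions and appears among the deaths and bleeding SAEs. The gap matters because the affected definition is the main one for the labelled safety endpoint, and because the stopping provisions name no other.

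No magnitude is claimed. The documents give neither an sICH rate nor the share of bleeds that are fatal before 22 h, and they do not state when treatment-related bleeding would occur. The conclusion rests on the literal wording and on the default reading that unqualified sICH means the first-named definition. This is an inexpensive correction to make, not a flaw that undermines the trial's safety oversight.

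**What to change.** Define the main sICH as PH2, local or remote, on the 22–36 h scan or on any earlier post-treatment scan done for clinical reasons, with the existing NIHSS and death criteria unchanged. A qualifying early bleed in a patient who dies before 22 h then counts.

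Alongside this:
- State that the randomised safety comparison and the DSMC reports use this count, so that sICH has one meaning in Safety monitoring.
- Reconcile the 24 h window for haemorrhagic transformation with the 22–36 h window for sICH in the Safety outcome section.
- Keep the strict 22–36 h version as a supplementary figure for comparison with published series.

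The cost is a sentence or two of text. The change asks for no additional scans or staff, and bleedings are already reported as SAEs. The small downside is that the main rate is no longer literally the published SITS-MOST definition, which the supplementary figure covers.
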